### Sample size

2.4

This pilot was sized to estimate feasibility parameters, not clinical efficacy. Using G*Power 3.1, sample sizes were derived from one-sided proportion tests (80% power, α=0.05) for retention and engagement; the one-sided test reflects the directional progression criteria, where only meeting or exceeding the thresholds is relevant. Thresholds were retention ⩾80% and engagement ⩾70%, yielding 62 and 56 participants, respectively; allowing for 20% dropout, the final target was 76 (38 per group). Both the directional hypothesis and the ⩾70% threshold are consistent with adherence benchmarks for feasibility pilots (27) and with retention and engagement rates reported in a comparable cardiovascular RPM intervention (e.g., 71%–94% sustained activity/survey completion over six months) (28).

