The primary objective of this pilot study is to evaluate the feasibility and acceptability of integrating PROMBot-HSM-AF, a chatbot-based platform for collecting PROMs and clinical parameters, into routine post-ablation follow-up care at a tertiary hospital. The specific aims, framed for the feasibility and pilot phase, are to: (1) quantify recruitment, retention, and engagement rates over the 3-month follow-up and compare each against pre-specified progression thresholds (retention ⩾80%, engagement ⩾70%), constituting the primary outcomes; and, as secondary, exploratory outcomes, (2) assess the usability and acceptability of the chatbot (patients) and of the clinical monitoring interface (healthcare professionals) at 3 months, using validated usability measures (System Usability Scale [SUS], Post-Study System Usability Questionnaire [PSSUQ]), behavioral indicators, and semi-structured interviews; and (3) evaluate the preliminary integration and data completeness of PROMs (e.g., Atrial Fibrillation Effect on Quality-of-Life [AFEQT]) collected via the platform over the 3-month follow-up, and explore between-group differences as hypothesis-generating estimates to inform a definitive trial.

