#### PROMBot-HSM-AF platform intervention

2.7.1

The research team will configure the PROMBot-HSM-AF chatbot and related remote monitoring platform, including definition of finite-state dialogue flows with AF-specific questions, message content, and input-validation rules. Pilot testing with 2–3 test users will also be conducted to identify usability issues and to verify delivery, latency, and data integrity. Health professionals involved in recruitment and follow-up will receive training on study procedures, including informed consent, platform registration, and use of the clinician interface to monitor incoming data.

Eligible patients undergoing AF ablation will be approached during their hospital stay. After receiving written study information, discussing questions, and providing informed consent, participants will complete a baseline assessment that will include demographics, medical history, recent clinical parameters (e.g., blood pressure and heart rate), and health-related quality of life (AFEQT, European Portuguese version) (13, 30). For participants randomized to the intervention group, PROMBot-HSM-AF will be set up before discharge by confirming WhatsApp is installed on the participant’s smartphone, registering the participant in the remote monitoring platform, linking their mobile number to PROMBot-HSM-AF, and sending a confirmatory message to verify correct enrollment. Patients (and caregivers, if applicable) will receive a brief demonstration and training, delivered by the study nurse, to ensure they can interact with the chatbot autonomously, and will also receive a leaflet with a brief explanation of the chatbot.

Participants in the intervention group will engage with PROMBot-HSM-AF via chatbot for 12 weeks. The chatbot will request self-reported health metrics (e.g., body mass, blood pressure, heart rate, step count, AF-related symptoms) and general well-being, supplemented with brief educational prompts (31). Participants who do not already own a validated blood pressure monitor will be provided with one at enrollment; device ownership is assessed during the baseline visit.

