#### Quantitative data

2.10.1

Participant characteristics and study outcomes will be summarized using descriptive statistics. Continuous variables (e.g., age, body mass, blood pressure) will be reported as means ± SDs or medians [IQR], depending on distribution, while categorical variables (e.g., sex, educational level, comorbidities) will be expressed as frequencies and percentages. Comparisons between groups will be performed using independent t-tests or Mann-Whitney U tests for continuous variables, and chi-square or Fisher exact tests for categorical variables, with 95% confidence intervals reported. The effect of the intervention on primary and secondary AF-related outcomes will be examined using regression models with and without adjustment for baseline covariates. Formal hypothesis testing is not the primary focus. All analyses will be conducted in R (version 4.5.0), with statistical significance defined as a two-sided p-value <0.05.

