If predefined feasibility criteria are met, findings from this pilot will inform the design of a definitive multi-center randomized controlled trial powered to detect clinically important differences in AF recurrence, complications, quality of life, and healthcare utilization. A full economic evaluation, including cost-effectiveness and budget impact analyses, would be incorporated to assess sustainability and inform health policy decisions. The qualitative findings will guide refinement of the intervention, particularly by optimizing alert thresholds, chatbot dialogue flows, and clinical monitoring interface features to minimize alert fatigue while maintaining safety, and by informing a risk-stratified approach that targets intensive digital monitoring to patients most likely to benefit (e.g., those with educational needs, poor symptom control, or elevated recurrence risk) rather than applying it uniformly.

If feasibility criteria are not met, qualitative data will illuminate specific barriers to implementation. Potential adaptations might include reduced prompt frequency, enhanced training protocols, integration with alternative messaging platforms if WhatsApp engagement proves insufficient, or simplified data collection focused on a core set of essential parameters. The modular design of PROMBot-HSM-AF enables iterative refinement of individual components based on empirical findings.

Beyond the immediate AF post-ablation context, findings may inform broader applications of chatbot-based monitoring in post-procedural care across cardiovascular and other medical specialties. The safety monitoring protocols and workflow integration strategies developed here may serve as templates for similar interventions. Furthermore, the structured PROMs and biosignal data collected through this platform will contribute to the CardioCausalAI project’s development of causal artificial intelligence models for predicting complications and optimizing clinical decision-making (48).

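### The 80% power in the sample-size section belongs to each threshold test alone; if both tests must be passed, power as designed is at most about 0.63 to 0.67, because engagement comes from only 38 patients.

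*Protocol article*

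**What the plan says.** The specific aims in the Introduction quantify recruitment, retention and engagement and "compare each against pre-specified progression thresholds (retention ⩾80%, engagement ⩾70%), constituting the primary outcomes". Recruitment is a primary outcome too, but has no threshold, so it is left out below.

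The Sample size section bases the numbers on "sample sizes were derived from one-sided proportion tests (80% power, α=0.05) for retention and engagement", and adds that "the one-sided test reflects the directional progression criteria, where only meeting or exceeding the thresholds is relevant". The result is given as "Thresholds were retention ⩾80% and engagement ⩾70%, yielding 62 and 56 participants, respectively". The final target, after a 20% dropout allowance, is 76, or 38 per group. The second proportion that each test needs (a true rate above the threshold, or a null rate below it) is not given.

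On the consequence, the Discussion says: "If predefined feasibility criteria are met, findings from this pilot will inform the design of a definitive multi-center randomized controlled trial". Its only other branch is that the criteria are not met. No sentence says how the two criteria combine, and no joint power is stated.

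On the source of the engagement data, the intervention section says: "Participants in the intervention group will engage with PROMBot-HSM-AF via chatbot for 12 weeks". Table 1 marks the engagement rate for the intervention arm only, and retention for both arms.

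**The concern.** A decision that needs two tests to succeed has lower power than either test alone, unless the two results coincide. The section powers each test at 80%, takes the larger sample size and stops there. A reader would take 80% as the chance that the pilot supports progression when the platform performs as planned.

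The second problem makes the first one worse. The engagement calculation asks for 56 participants, but only half of the 76 use the chatbot. The sample size was set by the larger requirement as if all participants supplied both outcomes. The engagement test therefore falls short of its stated power before any joint calculation is made, and it limits the joint power.

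At stake is how a miss would be read. If progression rests on the tests, a failure on engagement could easily be chance, and a stated 80% would make it look more informative than it is.

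**Working it through.** **Inputs.** From the Sample size section: one-sided α = 0.05, power 0.80 per test, thresholds 0.80 and 0.70, n = 62 and 56, total 76 with 38 per arm. From Table 1: engagement in the intervention arm only. Assumption: engagement is one binary result per patient, as a proportion test counted in participants implies.

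**Step 1. The plan's own figures.** The formula is n = [z(0.95)·√(p0(1−p0)) + z(0.80)·√(p1(1−p1))]² / (p1−p0)². One proportion is missing, so 62 and 56 cannot be reproduced; they can only be solved backwards.

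| Reading | Retention, n = 62 | Engagement, n = 56 |
|---|---|---|
| Threshold as null, normal approximation | true rate 91.4% | true rate 84.2% |
| Threshold as null, exact binomial | true rate 92.3% (reject at 56 or more) | true rate 85.2% (reject at 46 or more) |
| Threshold as alternative, normal approximation | null rate 65.8% | null rate 53.9% |

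For the final target, 62/0.8 = 77.5 and 62 × 1.2 = 74.4, so 76 lies between the two usual ways of allowing for dropout.

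**Step 2. Joint power at 62 and 56.** Under independence: 0.80 × 0.80 = 0.64. For any dependence, joint power lies between a + b − 1 and min(a, b), that is 0.80 + 0.80 − 1 = 0.60 and 0.80. With correlated normal test statistics it is 0.67 at correlation 0.3, 0.69 at 0.5 and 0.75 at 0.9.

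**Step 3. Joint power as designed, retention on 76 and engagement on 38.** The rates from step 1 are kept. In the exact test, rejection needs at least 67 of 76 retained and 32 of 38 engaged.

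| Reading | Retention power, 76 | Engagement power, 38 | Product | Upper bound |
|---|---|---|---|---|
| Threshold as null, normal | 0.882 | 0.629 | 0.555 | 0.629 |
| Threshold as null, exact | 0.933 | 0.670 | 0.625 | 0.670 |
| Threshold as alternative, normal | 0.873 | 0.647 | 0.565 | 0.647 |

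The upper bound needs no independence assumption: even with the strongest positive dependence, joint power cannot exceed engagement power. In the exact case the lower bound is 0.933 + 0.670 − 1 = 0.603.

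**Step 4. Dropout.** If 20% of the intervention arm leave and are not counted, 38 × 0.8 = 30.4, or about 30 patients. Exact engagement power is then 0.54 (reject at 26 or more), and 0.52 to 0.55 by the normal approximation.

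**Step 5. The other decision rule.** Suppose progression means an observed rate at or above the threshold: at least 61 of 76 and 27 of 38. At the normal-approximation rates of 91.4% and 84.2%, retention passes with probability 0.999 and engagement with 0.988. Rates exactly at the thresholds pass about half the time each (0.55 and 0.52).

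**The case against.** The strongest reply is that the criteria are thresholds, not significance tests. The aims compare each rate with its threshold, the Sample size section speaks of meeting or exceeding it, and the Quantitative data section says "Formal hypothesis testing is not the primary focus". On that reading the implied rates pass about 99% of the time on each criterion, and the joint-power figures do not apply. This stands as a limit on the finding. It does not rescue the stated 80%: the same section says the one-sided test reflects the progression criteria, and under an observed-rate rule that power is not a property of the decision at all.

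Three further points stand in part.

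- No sentence says both criteria are required. This is inferred from the plural and from the met/not-met split. It is the natural reading, and no either/or rule appears.
- The plan never assumes independence, and positive dependence is plausible, since a patient who leaves stops answering prompts. That weakens 0.64 as a single figure at 62 and 56. It does not affect the ceiling of about 0.63 to 0.67 as designed.
- Engagement is defined as a proportion of prompts answered, not as a yes/no per patient. The calculation here follows the sample-size section, which counts participants; another definition would change the numbers.

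A reader might infer that a platform performing as planned would be declared not feasible in about 4 of 10 such pilots. The documents do not support that. It requires a significance-test rule they do not state and true rates that are back-solved, not the plan's own. A reader might also infer that a miss mandates redesign, but the Discussion lists adaptations only as possibilities.

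**Conclusion.** The concern holds conditionally. The plan sets power per test and gives no joint figure. If both tests must be passed, the power of that decision at 62 and 56 is 0.64 under independence and 0.60 to 0.80 under any dependence. As designed, engagement power on 38 patients is about 0.63 to 0.67, and about 0.54 by exact test if 20% drop out and are not counted. Joint power cannot exceed engagement power; under independence it is about 0.55 to 0.63 with all 38 counted.

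This rests on true rates back-solved from 62 and 56, on one binary engagement result per patient, and on progression being judged by the tests. The shortfall in the engagement test does not depend on how the criteria combine: its calculation asks for 56 participants and the design supplies 38.

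**What to change.** In the Sample size section:

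1. State the assumed true rates for retention and engagement, and restate engagement power for the 38 intervention patients.
2. Give the joint power beside the two single-test figures, with the dependence assumed or the bounds.
3. State that both criteria are required, and whether each is judged by the one-sided test or by the observed rate. If by the observed rate, do not present 80% power as the property of the progression decision.

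The Discussion should refer to the same rule. The cost is a few sentences and a less favourable stated power; no added enrolment is needed. A third, inconclusive category between met and not met is optional and not part of the required change.

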### Study design

2.2

This study is a single-center, open-label, randomized controlled pilot (feasibility) trial with two parallel groups. Patients undergoing catheter ablation for AF will be randomly assigned 1:1 to chatbot-supported follow-up via the PROMBot-HSM-AF platform (intervention) or standard care (control). The control arm comprises structured discharge education and scheduled 1- and 3-month appointments without remote monitoring between visits (detailed under Procedures). The study flow diagram (Figure 1) represents the feasibility pathway.

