#### Control group

2.7.2

Participants allocated to the control group receive standard post-ablation care as delivered at Santa Marta Hospital, which includes structured discharge instructions with written educational materials about post-ablation care, scheduled follow-up appointments at 1 month and 3 months post-discharge, open access to the cardiology clinic telephone line during working hours for clinical concerns, and a 24-h hospital telephone service for urgent medical issues. Control group participants do not receive remote monitoring between scheduled appointments.

Both intervention and control groups complete identical standardized assessments at baseline (pre-discharge) and 3 months post-ablation. The timing of data collection activities is outlined in Table 1.

**Table 1 T1:** Schedule of enrollment, interventions, and assessments for the PROMBot-HSM-AF trial.

TRIAL PERIOD		Enrollment	Post-randomization				
Timepoint	Arm	⩽ day 0	Day 0	M1	M2	M3	M12
Target window		up to day 0	day 0	30±3 d	60±5 d	90±5 d	365±14 d
ENROLLMENT							
Eligibility screen	I+C	X					
Informed consent	I+C	X					
Randomization/allocation	I+C		X				
INTERVENTIONS							
PROMBot-HSM-AF	I			X	X	X	
Standard care	C		X	X	X	X	
PRIMARY OUTCOMES (FEASIBILITY)							
Recruitment rate	I+C	X	X				
Retention rate	I+C					X	
Engagement rate	I			X	X	X	
BASELINE CHARACTERISTICS							
Demographics	I+C		X				
AF history & comorbidities	I+C		X				
Procedure-related characteristics	I+C		X				
CLINICAL OUTCOMES (HOSPITAL-REPORTED)							
AF recurrence (AAD/cardioversion/repeat ablation)	I+C			X	X	X	X
Complications (readmission, ED visit, thromboembolism, major bleeding, tamponade)	I+C			X	X	X	X
All-cause mortality	I+C						X
Cardiology/internal-medicine consultations	I+C					X	X
Diagnostic tests (ECG, Holter)	I+C			X	X	X	X
PROMs							
AFEQT	I+C		X			X	
ESC quality-indicator items (weekly, rotating)	I			X	X	X	
Symptom checklist	I			X	X	X	
Medication adherence	I			X	X	X	
BIOSIGNALS							
Body mass	I			X	X	X	
Blood pressure	I			X	X	X	
Heart rate	I			X	X	X	
Step count	I			X	X	X	
ACCEPTABILITY & USABILITY							
Patient experience (SUS, PSSUQ, interview)	I					X	
Healthcare-professional experience (SUS, PSSUQ, interview)	HCP					X	

The schedule follows the SPIRIT figure convention (34).

M, month; d, days. Arm: I = intervention; C = control; HCP = healthcare professionals.

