#### Primary outcomes (feasibility)

2.9.1

The primary outcomes of this trial are feasibility parameters, including recruitment rate (eligible patients providing consent), retention rate (participants completing the 3-month follow-up), and engagement rate (proportion of chatbot prompts answered within 24 h) (36, 37).

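### The sample-size section asks for 56 participants for engagement, but only the 38 in the chatbot arm can supply engagement data, so the stated 80% power is unsupported for this outcome

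*Protocol article*

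**What the plan says.** Section 2.4 (Sample size) states that "sample sizes were derived from one-sided proportion tests (80% power, α=0.05) for retention and engagement". It sets the progression thresholds ("Thresholds were retention ⩾80% and engagement ⩾70" per cent) and gives the result: "yielding 62 and 56 participants, respectively; allowing for 20% dropout, the final target was 76 (38 per group"). No second proportion, whether null or expected rate, is given for either test. The nearest figure is a range from a comparable intervention, "71%–94% sustained activity/survey completion over six months", cited as consistent with the thresholds and not as a design alternative.

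Section 2.9.1 lists three primary feasibility outcomes, one of which is the "engagement rate (proportion of chatbot prompts answered within 24 h"). The Introduction's statement of aims makes the retention and engagement thresholds the only two numerical progression criteria.

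On who supplies the data:
- Section 2.2: patients "will be randomly assigned 1:1 to chatbot-supported follow-up via the PROMBot-HSM-AF platform (intervention) or standard care (control").
- Section 2.7.1: "Participants in the intervention group will engage with PROMBot-HSM-AF via chatbot for 12 weeks".
- Section 2.7.2: "Control group participants do not receive remote monitoring between scheduled appointments".
- Table 1 marks retention for both arms (I+C) and engagement for the intervention arm (I) alone.

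**The concern.** A requirement of 56 participants for engagement is followed by a single two-arm target of 76. The whole sample can serve retention. Only half of it can serve engagement, and that half is smaller than the number stated as necessary. A reader of section 2.4 would take both progression criteria to have 80% power.

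There is also a mismatch of unit. A one-proportion test on 56 participants gives each person a single yes or no. Section 2.9.1 defines engagement over the repeated prompts sent to each person, and the article gives no rule that would turn this into a participant-level yes/no.

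The Discussion makes progression to a definitive multi-center trial depend on the predefined criteria, so the stated support for one of the two numerical criteria should be correct.

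**Working it through.** **Inputs from the article.** One-sided α = 0.05, power 80%, engagement threshold 0.70, retention threshold 0.80, required sizes 62 and 56, dropout 20%, target 76, allocation 1:1, engagement in the chatbot arm only.

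**Step 1: the final target.** 62 × 1.2 = 74.4 (75 rounded up) and 62 / 0.8 = 77.5 (78 rounded up). The stated 76 lies between the two, so it is consistent with inflating the larger, retention-based number across both arms.

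**Step 2: can 56 be reproduced?** Not from the stated inputs, because the second proportion is missing. Using

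n = [(1.645·√(p0(1−p0)) + 0.842·√(p1(1−p1))) / (p1−p0)]²

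and searching for values that return about 56:
- p0 = 0.70, p1 = 0.84 gives 57.6; p1 = 0.8425 gives 55.4.
- p0 = 0.54, p1 = 0.70 gives 56.8; p0 = 0.5375 gives 55.1.

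These pairs are back-solved. They are assumptions, not figures from the article.

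**Step 3: participants available.** 76 / 2 = 38, and 38 / 56 = 68% of the stated requirement. This step needs no missing input.

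**Step 4: what 38 gives if 56 gives 80%.** The implied standardised effect is (1.645 + 0.842) / √56 = 0.332. Power at 38 is Φ(0.332 × √38 − 1.645) = Φ(0.403) = 66%.

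Power at n = 38 for the back-solved pairs:

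| p0 vs p1 | Normal formula | Exact binomial |
|---|---|---|
| 0.70 vs 0.84 | 62% | 59% |
| 0.70 vs 0.8425 | 63% | 61% |
| 0.54 vs 0.70 | 64% | 52% |
| 0.5375 vs 0.70 | 65% | 66% |

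The range is about 52 to 66%. Its width at the lower null is partly discreteness: moving the null from 0.54 to 0.5375 lowers the critical count from 27 to 26 and raises exact power from 52% to 66%.

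A larger effect, such as 0.50 vs 0.70, would give 38 participants 81% (normal) or 77% (exact). The required size would then be about 37, not 56, so that reading does not rescue the stated figure.

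**Step 5: engagement as a participant-level proportion.** Take each person's proportion of prompts answered and average over the 38. The between-person SD is not in the article; 0.20 to 0.30 is assumed. The 95% half-width is t(0.975, 37 df) × SD / √38, with t = 2.026:
- SD 0.20: 2.026 × 0.20 / 6.164 = 6.6 points.
- SD 0.30: 2.026 × 0.30 / 6.164 = 9.9 points.

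On this basis a one-sided one-sample t-test of 70% against 84.25% has power of about 89% (SD 0.30) to over 99% (SD 0.20). Against 80%, a 10-point difference, it has about 65 to 92%.

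**The case against.** The strongest reply is that this is a pilot. Section 2.4 says the trial was sized to estimate feasibility parameters, section 2.10.1 says formal testing is not the main focus, and no engagement test is named as the decision rule. This lowers the consequence. It does not withdraw the power statement, because the same section derives both sizes from tests at 80% power and defends the one-sided direction by the progression criteria.

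A second reply is that the true power for engagement may be adequate. That stands: the participant-level mean in step 5 could exceed 80% with 38 people. A reader might infer from 52 to 66% that the outcome is underpowered. The article does not support that, since those figures rest on unstated alternatives and on a yes/no model that does not match the outcome.

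Three further inferences are tempting but not supported:
- **That dropout cuts the engagement sample to about 30** (38 × 0.8 = 30.4). Section 2.7.1 records unanswered prompts as missing after 24 h, while section 2.9.1 counts the proportion of prompts answered. Someone who stops replying may still contribute a low value. The article does not settle how withdrawals are counted, so 38 is the figure to use, as an upper limit.
- **That the interval will be too narrow because prompts are pooled as independent.** The article never proposes such an analysis, and handling of clustering may properly sit in an analysis plan not shown.
- **That the plan checked 56 against the total of 76.** No such comparison is written. What can be said is that the engagement requirement is not reconciled with the size of its arm.

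**Conclusion.** The point holds in a limited form. Section 2.4 requires 56 participants for engagement at 80% power, and the design provides at most 38. That follows from the allocation and Table 1 alone, and a two-group reading of the 56 does not help because controls have no engagement value. The stated power for this primary progression outcome is therefore not supported by the plan's own calculation.

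The size of the gap, 52 to 66% instead of 80%, is illustrative. It takes 56 as correct and keeps the one-proportion model. The precision of ±6.6 to 9.9 points rests on an assumed SD of 0.20 to 0.30. The retention calculation is not affected by this point, since retention is measured in both arms.

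**What to change.** Keep the target of 76. In section 2.4:
1. Let the 62 and the 80% power statement apply to retention, measured in both arms.
2. Remove the 56 and the 80% power claim for engagement.
3. State that engagement will be estimated in the 38 chatbot participants as the mean of individual response proportions, and compared with the 70% threshold.
4. Give the expected precision: a 95% CI half-width of about ±6.6 to 9.9 points for an assumed between-person SD of 0.20 to 0.30, with the SD labelled as an assumption.

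The cost is a less favourable stated figure for engagement. No extra patients are needed, and randomisation, intervention and thresholds stay as they are.

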In the first month, chatbot interactions will occur daily, focusing on post-ablation symptom surveillance and medication adherence. After that, the cadence will taper to reduce burden in later weeks while maintaining essential monitoring. Chatbot prompts will remain open for 24 h, after which nonresponses will be recorded as missing data. A study nurse or physician will review patient entries weekly and may proactively contact participants reporting concerning symptoms or lapses in engagement. PROMBot-HSM-AF will not replace routine follow-up; all patients will continue standard clinical care, with chatbot data available to the study clinical team to complement or inform consultations at the treating cardiologist’s discretion.

At the end of the 3-month follow-up period, all participants will undergo post-intervention assessments during a routine hospital visit. If necessary, these assessments will be conducted via secure videoconference. The PROMs will focus on the effect of AF on health-related quality of life. Participants in the intervention group will also complete validated measures of usability and perceived usefulness. They will also take part in a brief semi-structured interview to share their experience of using the chatbot. Semi-structured interviews will also be conducted with healthcare professionals directly involved in patient care (e.g., cardiologists, nurses, and technicians). These interviews are intended to elicit qualitative insights regarding their experience with the chatbot-based intervention, as well as their perceptions of its usability, clinical relevance, and impact on workflow integration.

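### The engagement test is sized at 56 participants, but only the 38 chatbot-arm patients can have an engagement rate, so the stated basis for 80% power is not met

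*Protocol article*

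**What the plan says.** Section 2.4 (Sample size) states that "sample sizes were derived from one-sided proportion tests (80% power, α=0.05) for retention and engagement". It names the progression thresholds ("Thresholds were retention ⩾80% and engagement ⩾70"%) and reports the result as "yielding 62 and 56 participants, respectively; allowing for 20% dropout, the final target was 76 (38 per group". It gives no second proportion for either test and does not say whether each threshold is the null or the alternative.

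Other sections settle who can supply the engagement endpoint:

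- Section 2.2: patients "will be randomly assigned 1:1 to chatbot-supported follow-up via the PROMBot-HSM-AF platform (intervention) or standard care (control").
- Section 2.9.1: the outcome is the "engagement rate (proportion of chatbot prompts answered within 24 h").
- Section 2.7.1: "Participants in the intervention group will engage with PROMBot-HSM-AF via chatbot for 12 weeks".
- Section 2.7.2: "Control group participants do not receive remote monitoring between scheduled appointments". Table 1 marks retention for both arms and engagement for the intervention arm only.

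**The concern.** The two-arm total of 76 is presented as covering both calculations. It suits retention, which every randomised patient can contribute to. It does not suit engagement, for which half of the 76 have no data by design. The plan therefore claims 80% power for a primary outcome using a number of patients that the design cannot supply.

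Engagement is one of only two outcomes with a numeric progression threshold (Introduction, aim 1), and the only one specific to the chatbot. The Discussion counts predefined success criteria as a strength and makes a definitive trial depend on meeting them. A reader of section 2.4 would believe that the engagement criterion is assessed with a one-in-five risk of missing a chatbot that performs as assumed. The design does not support that belief as stated.

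**Working it through.** **Inputs from the article.** One-sided alpha 0.05, 80% power, engagement threshold 70%, 56 participants required for engagement and 62 for retention, 20% dropout, 76 in total, 1:1 allocation, engagement in the intervention arm only.

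**Step 1: head count (no assumption needed).** Chatbot-arm patients: 76/2 = 38. Shortfall against 56: 18, even with no dropout. If dropouts are excluded, 38 × 0.8 = 30.4, about 30. The total of 76 follows from the retention figure: 62/0.8 = 77.5 (78) and 62 × 1.2 = 74.4 (75), with 76 between them.

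**Step 2: the plan's own 56.** It cannot be derived from the stated inputs, because one proportion is missing. It can only be matched by back-solving. With 70% as the null, the alternative that gives 80% power at n = 56 is 0.842 (normal approximation) or 0.852 (exact binomial, at least 46 of 56 needed). With 70% as the alternative, a null of 0.54 gives 57 (normal).

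**Step 3: power for a yes/no outcome per patient.** The normal-approximation formula is

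power = Φ{[√n (p1 − p0) − 1.645 √(p0(1 − p0))] / √(p1(1 − p1))}.

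For p0 = 0.70, p1 = 0.842, n = 38: [6.164 × 0.1418 − 1.645 × 0.4583]/0.365 = 0.33, and Φ(0.33) ≈ 0.63.

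Without choosing proportions, power can be scaled from 80% at n = 56: Φ(2.487 √(n/56) − 1.645). This gives Φ(0.40) = 0.66 at 38 and Φ(0.175) = 0.57 at 30.

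| Assumption | n = 56 | n = 38 | n = 30 |
|---|---|---|---|
| Scaling from 80% at 56 | 80% | 66% | 57% |
| 0.70 vs 0.842, normal | 80% | 63% | 52.5% |
| 0.70 vs 0.852, exact (46/56, 32/38, 26/30 to pass) | 80% | 67% | 54% |
| 0.54 vs 0.70, normal | 79% | 64% | 55% |
| 0.54 vs 0.70, exact | 79% | 52% | 43% |

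**Step 4: power for a mean per-patient share of prompts.** The article gives no between-patient SD, so these are assumed values. For a mean of 0.84 the SD cannot exceed √(0.84 × 0.16) = 0.37, which is the yes/no case. A one-sided one-sample t test of 0.84 against 0.70 gives:

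| Assumed SD | Power, n = 38 | Power, n = 30 |
|---|---|---|
| 0.25 | 96% | 91% |
| 0.30 | 88% | 80% |
| 0.35 | 78% | 69% |

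**Step 5: precision for a yes/no outcome.** The 95% half-width is 1.96 √(p(1 − p)/n). At 70%: 14.6 points with 38, against 12.0 with 56. At 84%: 11.7 points with 38.

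**The case against.** Three arguments limit the point.

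*The pilot is for estimation.* Section 2.4 says that the aim is to estimate feasibility, and section 2.10.1 plays down formal testing. If progression means only that the observed rate reaches 70%, a true rate of 84% would almost always pass with 38 patients: for a yes/no outcome, P(at least 27 of 38) is about 99%. This stands, and it lowers the consequence. It does not remove the mismatch, because the same paragraph of 2.4 justifies the number by power, alpha and a one-sided test.

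*The endpoint is a share of prompts.* Each patient supplies a graded rate over 12 weeks, so 38 patients may be enough. This also stands: step 4 shows power on either side of 80%. A reader might infer that power is simply 53–67%, or that the loss is the same whatever the unit. The documents support neither. The missing 18 patients do not depend on the unit, but the percentages do. Counting prompts would not restore the 56 either, because section 2.4 counts participants and prompts are clustered within at most 38 of them.

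*Dropouts need not leave the engagement denominator.* All 38 are to be sent prompts. Section 2.7.1 says "Chatbot prompts will remain open for 24 h, after which nonresponses will be recorded as missing data", and nothing removes patients who drop out. So 38 is the firm ceiling, and 30 is one reading, suggested by the plan's own dropout allowance.

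A reader might also multiply the powers for retention and engagement into a joint chance of passing. The article does not say that both must pass a significance test, and independence is doubtful because a patient who drops out stops answering prompts.

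**Conclusion.** The mismatch is certain: 56 participants are stated as needed for engagement, at most 38 can contribute, and no section reconciles the two. The stated basis for 80% power on engagement is therefore not met by the design.

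The size of the loss is conditional. It is about 63–67% power with 38 patients, and about 53–57% with 30, if three things hold: 56 gives 80%, each patient counts as one yes/no outcome, and 70% is the null. With 0.54 against 0.70 and an exact test it falls to 52% and 43%. For a mean per-patient share of prompts, power cannot be stated without an SD and could exceed 80%.

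This should be corrected before results are read against the threshold. In a feasibility pilot, where the remedy is wording, it does not call the trial's conduct into question.

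**What to change.** Keep 76 patients. In section 2.4:

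1. State that engagement is assessed in the 38 chatbot-arm patients, and remove the implication that the total of 76 covers the 56.
2. State the unit of the engagement endpoint (a yes/no classification per patient, or a mean per-patient share of prompts), the null and the assumed alternative. For a mean share, also state the assumed SD. Say whether patients who drop out stay in the denominator.
3. Restate power for n = 38 on that basis, or replace it with the expected 95% confidence interval half-width. For a yes/no outcome this is about ±15 points at 70% and ±12 points at 84%; for a mean share it follows from the assumed SD.
4. Report the 70% criterion together with its interval.

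The cost is wording in section 2.4 and the matching analysis text, and the stated power for engagement may become less favourable. No recruitment is added. For comparison, supplying 56 evaluable chatbot patients after 20% dropout would take 56/0.8 = 70 per arm, or 140 in total, which is not proposed for a pilot.
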